## Abstract

**Background:**

The World Health Organization has estimated that by 2030, chronic obstructive pulmonary disease will be the third leading cause of death worldwide. Most knowledge of chronic obstructive pulmonary disease is based on studies performed in Europe or North America and little is known about the prevalence, patient characteristics and change in lung function over time in patients in developing countries, such as those of Latin America. This lack of knowledge is in sharp contrast to the high levels of tobacco consumption and exposure to biomass fuels exhibited in Latin America, both major risk factors for the development of chronic obstructive pulmonary disease. Studies have also demonstrated that most Latin American physicians frequently do not follow international chronic obstructive pulmonary disease diagnostic and treatment guidelines. The PRISA Study will expand the current knowledge regarding chronic obstructive pulmonary disease and risk factors in Argentina, Chile and Uruguay to inform policy makers and health professionals on the best policies and practices to address this condition.

**Methods/Design:**

PRISA is an observational, prospective cohort study with at least four years of follow-up. In the first year, PRISA has employed a randomized three-staged stratified cluster sampling strategy to identify 6,000 subjects from Marcos Paz and Bariloche, Argentina, Temuco, Chile, and Canelones, Uruguay. Information, such as comorbidities, socioeconomic status and tobacco and biomass exposure, will be collected and spirometry, anthropometric measurements, blood sampling and electrocardiogram will be performed. In year four, subjects will have repeat measurements taken.

**Discussion:**

There is no longitudinal data on chronic obstructive pulmonary disease incidence and risk factors in the southern cone of Latin America, therefore this population-based prospective cohort study will fill knowledge gaps in the prevalence and incidence of chronic obstructive pulmonary disease, patient characteristics and changes in lung function over time as well as quality of life and health care resource utilization. Information gathered during the PRISA Study will inform public health interventions and prevention practices to reduce risk of COPD in the region.

## Background

Although chronic pulmonary diseases, including chronic obstructive pulmonary disease (COPD), are believed to be one of the leading causes of morbidity and mortality in the Southern cone, few studies have described the prevelance and patient characteristics in this region and no study has described COPD trends over time. The World Health Organization (WHO) has predicted a rise in the mortality from COPD, from the fourth leading cause of death in 2004 to the third in 2030, largely attributable to rising tobacco consumption and biomass fuel exposure, both major risk factors for COPD and overwhelmongly prevalent in developing countries[1-3].

Variable definitions, under-recognition and under-diagnosis of COPD and its exacerbations have made it difficult to quantify prevalence, morbidity and mortality based on available data, particularly in low and middle-income countries[4,5]. An accurate estimate of the worldwide burden of COPD remains unknown[6,7]. The Latin American Project for the Investigation of Obstructive Lung Disease (PLATINO) examined the prevalence of COPD by pre- and post-bronchodilator spirometry among persons over age 40 in five major Latin American cities and found that the overall prevalence (95% CI) of COPD varied from 7.8% (5.9-9.7) in Mexico City to 19.7% (17.2-22.1) in Montevideo and was notably higher in older subjects and males. The reasons for the range of prevalence are unclear[8]. Outside of this study, the reliability of COPD prevalence estimates is questionable. For example, there are no population-based studies of COPD prevalence in Argentina, but estimated prevalences range from 5 to 8%[9]. Interestingly, these numbers are lower than the prevalences demonstrated by the PLATINO study, and Argentine adults have among the highest mean tobacco consumption in the region (58.1 pack-years)[5].

Moreover, studies have shown rates of tobacco consumption amongst younger generations in Latin America to be shocking. For example, in Argentina, Chile and Uruguay, 25.8%, 39.2% and 22.9%, respectively, of 15-18 years olds smoke compared with WHO estimates of 13.2% of people aged 15-18 worldwide[10-12]. These numbers support the idea that Latin America is early in its COPD epidemic and the prevalence and associated costs will only continue to rise as populations age, unless appropriate preventive and treatment measures are instituted.

In 2010, the National Heart, Lung and Blood Institute (NHLBI) funded an observational prospective cohort study, led by the Instituto de Efectividad Clinica y Sanitaria (IECS) in Buenos Aires, Argentina in parnership with Tulane University School of Public Health and Tropical Medicine in New Orleans, Louisiana, U.S.A, the Universidad de la Frontera in Temuco, Chile, and the Universidad de la República, in Montevideo, Uruguay, to determine the prevalence and incidence of COPD and describe patient characteristics and change in lung function over time, as well as quality of life and health care resources utilization. Spirometry will be performed and questionnaires administered to 6,000 subjects from Marcos Paz and Bariloche, Argentina, Temuco, Chile, and Canelones, Uruguay to further knowledge of COPD in these mid-sized cities representing the Southern cone of Latin America.

## Methods/Design

The PRISA study is an observational, prospective cohort study with at least 4 years of follow-up. Subjects 45-75 years of age are being recruited using a multistage cluster sampling method. The study is composed of two phases. In the first phase, baseline data will be collected regarding exposure to risk factors and prevalence of COPD. In the second phase, annual follow-up data will be obtained to determine the rate of incident COPD, the association between exposure and development of COPD, and the rate of decline in lung function exhibited by COPD subjects identified in the first phase. Inclusion criteria were men and women aged 45-75 years of age, permanent resident at one of the study locations for at least six months each year and willingness to offer written consent. Exclusion criteria were an expressed intenton to relocate within the next four years, inability to respond to the questionnaire due to cognitive impairment or language difficulty, active tuberculosis, pregnancy, or history of detached retina and cardiac infarction or ocular, thoracic or abdominal surgery within prior six weeks (contraindications to spirometry testing). A total of 6,000 non-institutionalized, mainly urban, (1,500 participants per site), men and women will be recruited from Bariloche and Marcos Paz, Argentina, Temuco, Chile, and Canelones, Uruguay.

### Sampling Procedure

A randomized, three-staged, stratified, cluster sampling strategy was usedin order to select a representative sample of the general population aged 45 to 75 years of age. The first stage selected 60 census enumeration areas using probability proportional to size, with implicit stratification by socioeconomic level of the enumeration area. The second stage selected 40 households from each enumeration area using systematic sampling. The third stage selected one household member between 45-75 years of age for the study. The final sampling was stratified by gender, with 50% men and 50% women, and age distribution based on recent population census data[13,14](Figure 1).

**Figure 1 F1:**
[figure not shown]
**Sampling procedure**.

### Recruitment Plan

Participants identified by the sampling procedure are invited to participate through a letter from the site institution. The interviewer makes contact with the household and arranges a home visit, to collect questionnaire data, and a clinic visit. At the clinic visit, physical measurements, pre and post-bronchodilator spirometry and electrocardiogram (EKG) are performed and overnight, fasting blood samples are collected. To minimize non-participation and the potential for bias in the results, specific measures, such as travel assistance or home assessment, flexibility of appointment times, feedback of blood test and examination results and participation of local health professionals, non-governmental organizations and local authorities, have been involved to facilitate and encourage the participation of those selected for the study.

### Primary Outcome

The primary outcome for phase one of the study is the prevalence of COPD, as defined by the Global initiative for Obstructive Lung Disease (GOLD). The lower limit of normal (LLN) values for these populations will be calculated, using the American Thoracic Society (ATS) and European Respiratory Society (ERS) guidelines. The primary outcome for the four-year follow-up is the change in lung function. Secondarily, the incidence of COPD will be calculated. These criteria are listed in Table 1.

**Table 1 T1:** Spirometric criteria for the definition of COPD

Spirometry Criteria	Definition
GOLD[1]	Post-bronchodilator forced expiratory volume in the first second (FEV1)/forced vital capacity (FVC) < 70 and FEV1 < 80% of predicted value
ATS[28,29]	Post-bronchodilator FEV1/FVC below the LLN and FEV1 < 100% of predicted value
ERS[30]	Post-bronchodilator FEV1/FVC < 88% of the predicted value for men and < 89% for women

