Spirometric measurements will be performed with identical, portable, battery operated, ultrasound transit-time based EasyOne^™ ^spirometers (Medical Technologies, Chelmsford, Massachusetts and Zürich, Switzerland). Calibration will be checked daily with a three-liter syringe. Test results will be stored in the spirometer memory and downloaded weekly to a central computer. Trained professionals will first administer a questionnaire to determine patient eligibility, as described above. Trained personnel will then perform spirometry following ATS guidelines. Spirometry will be conducted with subjects in the seated position, wearing a nose clip and using a disposable mouthpiece. Subjects will perform up to eight forced expiratory maneuvers with forced vital capacity (FVC) and forced expiratory volume in the first second (FEV1) reproducible within 150 ml. A beta-agonist bronchodilator, Albuterol 200 ug, will be administered and repeat spirometry will be performed 15 minutes later, using the same criteria. All field methods have been tested in pilot studies at each site.

All health care professionals involved in the study have participated in a two-day spirometry and questionnaire training led by the main study coordinator, a pulmonologist from the coordinating center ([name]). The spirometry course focused on the acceptability and reproducibility of a pulmonary function test and the factors associated with an unacceptable spirometry test. The technicians were certified if they were able to perform 10 pulmonary function tests that met the 2005 ATS/ERS criteria.

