### Statistical Analysis

General characteristics of the population will be described. For continuous variables, mean and median, range, standard deviation, and/or quartile range will be calculated according to the distribution of each variable. In the case of categorical variables, absolute and relative frequencies will be calculated.

In order to determine the prevalence and incidence of COPD and patient characteristics and risk factors, the design effect of the first stage unit of sampling will be considered. Weighting will be based on the relation between the number of individuals included in the study and the population size and composition of each site according to the most recent census data. Likewise, the analysis will be carried out by socioeconomic strata, gender and age categories.

To assess the association between risk factors and COPD, linear regression and simple and multiple logistical regressions will be used according to the nature of the response variables. Continuous variables that are not normally distributed will be evaluated by the application of transformations and categorizations wherever applicable[25]. The secular trends in risk factors over time will be evaluated with methods of statistical analysis that take into account the correlation between repeated measures. To evaluate the changes in risk factors over time by sub-groups of interest, generalized estimation equations will be used. To estimate the rate of accumulated COPD incidents, the Kaplan-Meir method will be used. The log rank test will be used to compare the differences between the curves of accumulated incidence events. The log rank test of trend will be applied to analyze the relationship between the accumulated risk by quartile group or by created groups of interest. In order to quantify the relationship between risk factors and the incidence of COPD, the Cox Proportional Hazards method will be used. Potential confounders and interactions will be explored.

Appropriate diagnostics will be carried out to test goodness of fit, co-linearity, and atypical observations in each model. In all cases, fulfillment of assumptions in the model by means of exploration of residual behavior will be verified. Statistical analysis software STATA 10.0 and SAS 9.0 will be used[26,27].

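### Four-year COPD incidence is a one-way crossing of hard spirometric thresholds, so test-to-test variation probably inflates it, by an amount the article gives no means to judge

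*Protocol article*

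**What the plan says.** Under Primary Outcome, the article makes change in lung function the primary four-year outcome and then adds: "Secondarily, the incidence of COPD will be calculated. These criteria are listed in Table 1". Table 1 gives three definitions:

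- GOLD: "Post-bronchodilator forced expiratory volume in the first second (FEV1)/forced vital capacity (FVC) < 70 and FEV1 < 80% of predicted value"
- ATS: "Post-bronchodilator FEV1/FVC below the LLN and FEV1 < 100% of predicted value"
- ERS: "Post-bronchodilator FEV1/FVC < 88% of the predicted value for men and < 89% for women"

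The GOLD ratio is a fixed number, and the other two use the lower limit of normal or a percentage of predicted. All three are hard yes/no limits. The article does not say which one defines incidence, and this point does not depend on the choice.

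Under Statistical Analysis: "To estimate the rate of accumulated COPD incidents, the Kaplan-Meir method will be used". Log rank tests and Cox models follow.

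Under Instruments, each assessment has one post-bronchodilator session, with FVC and "forced expiratory volume in the first second (FEV1) reproducible within 150 ml".

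On timing, the Abstract says "In year four, subjects will have repeat measurements taken", while Methods/Design says "annual follow-up data will be obtained to determine the rate of incident COPD". Whether spirometry itself is annual is not stated.

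**The concern.** A person whose true value lies close to a threshold can test on either side of it on different days without any change in the lungs. If nobody changed at all, chance entries into COPD and chance exits from it would balance. A first-event analysis counts only the entries. A baseline case who later tests negative was never at risk of the event, so that exit appears nowhere.

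COPD incidence is secondary, but it is a stated aim of the study and of its second phase, and the Discussion says the results should inform legislation and prevention. The Cox models for risk factors use the same events. What is at stake is whether the published rate can be read as disease onset.

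**Working it through.** **The plan's own figure.** There is none to reproduce. The article gives no expected incidence, between-visit error or rate of decline. Table 2 concerns sample size for proportions and does not bear on this point.

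**Inputs from the article.** The Table 1 GOLD rule (both parts required), first-event estimators, one post-bronchodilator session per assessment, and 6,000 participants.

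**Assumed inputs (none from the article).**
- True FEV1/FVC: mean 77.5, SD 6. True FEV1 % predicted: mean 95, SD 15. Correlation 0.5.
- Between-visit error SD: 1 to 4 ratio points and 2 to 8 FEV1 points (error correlation 0.4).
- Mean yearly change: −0.2/−0.2 (slow), −0.3/−0.5 (medium) and −0.5/−1.0 (faster), in ratio/FEV1 points, with spread between people.

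**Step 1: gross incidence, one baseline and one year-four test.** Gross incidence is the number of new cases divided by those testing negative at baseline. At middle noise (SD 2 and 4):

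| Decline | True | Recorded | Recorded/true |
|---|---|---|---|
| Slow | 1.78% | 3.06% | 1.72 |
| Medium | 2.64% | 3.89% | 1.48 |
| Faster | 4.77% | 5.75% | 1.20 |

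Over all noisy scenarios the ratio ran from 1.04 (low noise, faster decline) to 2.82 (high noise, slow decline). A rule on the ratio alone at 70 gave 1.05 to 2.80, so the two-part rule is not the cause. Runs under other assumed populations gave 1.10 to 2.47, 1.12 to 2.83 and 1.3 to 2.8.

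**Step 2: no decline at all.** With error SDs of 1/2 to 3/6, 1.0% to 2.9% still became incident by year four.

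**Step 3: annual tests, first crossing counted.** The ratio rose to between 1.27 and 6.69. At middle noise it was 3.33, 2.61 and 1.87 for slow, medium and faster decline.

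**Step 4: net incidence.** Net = gross − (share of baseline cases that revert) × p/(1 − p), where p is observed baseline prevalence. At middle noise:
- Slow: 3.06 − 29.05 × 5.08/94.92 = 3.06 − 1.55 = 1.51% (true 1.78%; net/true 0.85).
- Medium: 3.89 − 24.12 × 5.15/94.85 = 3.89 − 1.31 = 2.58% (true 2.64%; 0.98).
- Faster: 5.75 − 17.13 × 5.10/94.90 = 5.75 − 0.92 = 4.83% (true 4.77%; 1.01).

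Under other assumptions net/true was mostly 0.95 to 1.06, but it fell to 0.73 to 0.83 where decline was slow and varied between people. A further set gave 0.64 to 1.04. Net falls short because some people truly recover across the line and are subtracted.

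**In people (medium decline, middle noise, full retention, unweighted).** 6,000 × 0.9485 = 5,691 test negative at baseline, and 5,691 × 0.0389 = 221 are recorded as new. Reversions are 309 × 0.2412 = 75. Net is 221 − 75 = 146, or about 2.6%. True onsets are 6,000 × 0.9529 × 0.0264 = 151. Of the 221, about 47% are not truly below the line at year four and about 32% are genuine onsets.

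**Step 5: confirmation.** Requiring a second positive test at year four, at middle noise, gave 1.4% against a true 1.8% (slow) and 1.9% against 2.6% (medium).

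**The case against.** The strongest reply is that this is a condensed article. Confirmation rules, reversion and adjudication commonly sit in the full protocol or analysis plan, and threshold spirometry with Kaplan-Meier and Cox is a conventional cohort choice. This stands in part: a confirmation rule may exist elsewhere, and its absence here is weak evidence. But the point does not rest on silence. The article states both the case definition and the estimators, and in their ordinary use the two together count one way.

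Three stronger readings are tempting, and the article supports none of them.

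- **Incidence is substantially overstated.** The size comes wholly from assumed error and decline. At low noise with faster decline the excess is 4%.
- **The 150 ml limit shows errors of about 4 ratio points.** It is a within-session acceptance limit, not a between-visit error. 150/3,500 = 4.3 points puts all the error on FEV1 at an assumed FVC of 3.5 L. If FEV1 and FVC move together, 2.45/3.50 = 70.0 becomes 2.30/3.35 = 68.7, a shift of 1.3 points.
- **Risk-factor associations are diluted.** False crossings depend on baseline distance from the line, which exposure can itself shift. With an assumed exposed group 3 ratio points and 4.5% predicted lower at baseline and the same decline, false events were 1.59 to 1.68 times as frequent in the exposed. The risk ratio was not diluted: 1.57 to 1.65 observed against 1.55 to 1.60 true. If exposure acts only on decline, dilution can occur.

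**Conclusion.** The point holds in limited form. Hard thresholds analysed by first-event methods bias COPD incidence upward whenever there is between-visit error, and every noisy scenario agreed on that direction for gross incidence. With one baseline and one year-four test the factor was about 1.0 to 2.8, and 1.20 to 1.72 at middle noise. With annual tests and first-crossing counting it was larger. These ranges describe the assumptions tried and are not bounds; the article supplies neither of the two quantities that fix the size. Risk-factor estimates for incident COPD may be distorted, in a direction that depends on how exposure relates to baseline lung function. Incidence is secondary, and the primary outcome, a continuous change, is not subject to threshold crossing. A confirmation rule in the full protocol would change the assessment, though such a rule brings a bias of its own.

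**What to change.** 1. Among people with both tests, report transitions in both directions. Beside gross incidence give the net figure, (new cases − reversions) / (number without COPD at baseline), as a sensitivity estimate. Say plainly that gross tends to be too high, and that net is about right or too low. Neither should be called unbiased.
2. Reconcile the Abstract with Methods/Design on whether spirometry is repeated annually or only in year four.
3. If it is annual, add an analysis that counts a case only when the next scheduled test also meets the criterion. Keep it as a sensitivity analysis: confirmation can undercount, and cases first seen at the last visit stay unconfirmed. With year-four testing only, it cannot be applied.

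The cost is some wording and a little extra analysis, with no new visits or tests. The downsides are a less favourable and less certain incidence figure, and a net figure that differential death or dropout of baseline cases can distort. The net figure also gives no person-level event for the Cox models, so it does not repair the risk-factor analysis. The possible distortion there should be stated when those results are reported.

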## Discussion

Despite the burden of COPD in Latin America, there is limited knowledge of the prevalence and incidence of COPD, patient characteristics and provider prescribing regimens in this region. Although the PRISA study is not representative of the total population in Latin American, it is, to our knowledge, the first population-based cohort study addressing knowledge gaps and informing public health policy-making on the impact of COPD in Argentina, Chile and Uruguay.

The close cooperation between experienced researchers in Argentina, Chile, Uruguay, and Tulane University in the USA is a study strength. Methodology to estimate prevalence is similar to that used in the PLATINO study, which will allow comparison of data between the Latin American countries studied in the PLATINO study and the baseline phase of the PRISA study. The PRISA study, however, has the advantage of being the first longitudinal study of pulmonary function in Latin America. In addition, questionnaires used in the HCHS/SOL study[19], a cohort study performed on Hispanic population in the USA will be also used in the PRISA study, allowing additional comparison between PRISA study subjects and the Latin American and Hispanic communities in the United States.

It is clear that chronic pulmonary diseases, including COPD, are leading causes of morbidity and mortality worldwide. Our study will provide important information about the epidemiology of COPD in select cities in Argentina, Chile and Uruguay. In the first phase of the study, it will describe COPD prevalence and associated risk factors, socioeconomic status, concurrent medical history, patient characteristics and physician prescribing trends. In the second phase, it will describe the decline in lung function over time, COPD incidence and any changes in patient characteristics and physician prescribing trends. This information is paramount to the development of appropriate public health legislation and preventive interventions.

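### The primary COPD definition requires FEV1 <80% predicted as well as a low ratio, so people with a low ratio but FEV1 at or above 80% are baseline non-cases and, unless the risk set is defined otherwise, can later count as incident COPD

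*Protocol article*

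**What the plan says.** Under Primary Outcome, the protocol article states: "The primary outcome for phase one of the study is the prevalence of COPD, as defined by the Global initiative for Obstructive Lung Disease (GOLD"). Table 1 gives the GOLD criterion as "Post-bronchodilator forced expiratory volume in the first second (FEV1)/forced vital capacity (FVC) < 70 and FEV1 < 80% of predicted value". The 70 is read here as a ratio of 0.70.

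Table 1 also lists an ATS rule, "Post-bronchodilator FEV1/FVC below the LLN and FEV1 < 100% of predicted value", and an ERS rule, "Post-bronchodilator FEV1/FVC < 88% of the predicted value for men and < 89% for women". The FEV1 condition is thus below 80% in the first row, below 100% in the second, and absent from the third.

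The four-year primary outcome is change in lung function. Incidence follows it: "Secondarily, the incidence of COPD will be calculated. These criteria are listed in Table 1". Methods/Design gives the purpose of follow-up: "annual follow-up data will be obtained to determine the rate of incident COPD, the association between exposure and development of COPD". The Statistical Analysis section assigns Kaplan-Meier and log-rank methods to cumulative incidence and Cox models to its risk factors. The article does not say who is at risk for incidence or which row of Table 1 governs it.

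**The concern.** The GOLD row joins a test for obstruction (the ratio) to a cut on severity (FEV1 below 80% predicted), while the result is called prevalence of COPD without qualification. Two things follow.

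- **Prevalence.** The reported figure cannot exceed the ratio-only figure, and is lower whenever anyone has a low ratio with FEV1 at or above 80%. A reader comparing the three rows cannot tell whether a difference comes from the ratio rule or from the FEV1 condition.
- **Incidence.** If the at-risk set is simply everyone who is not a baseline case, it includes people whose ratio was already low. Some will be counted as new COPD only because FEV1 crossed 80%. Cumulative incidence and hazard ratios for tobacco or biomass exposure would then combine the onset of obstruction with the worsening of existing obstruction, and a risk factor may act differently on the two.

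**Working it through.** The plan states no figure for this point, so there is none to reproduce. The first step reads Table 1 directly. The others rest on assumptions, which are stated.

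**1. Applying the rule.** Take ratio 0.65 and FEV1 85% predicted at baseline. The ratio condition is met and the FEV1 condition is not, so this is a GOLD non-case. At follow-up the ratio is still 0.65 and FEV1 is 79%. Both conditions are now met, so this is a GOLD case. The ratio has not changed. The direction of the effect needs no assumption.

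**2. Share of low-ratio people left out of prevalence.** Assume ratio mean 0.77, SD 0.06; FEV1 mean 95% predicted, SD 15; bivariate normal with correlation ρ from 0 to 0.6.

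- P(ratio <0.70) = Φ((0.70 − 0.77)/0.06) = Φ(−1.167) = 12.17%.
- P(FEV1 <80%) = Φ((80 − 95)/15) = Φ(−1) = 15.87%.
- Share left out = 1 − P(both)/P(ratio <0.70).

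| ρ | P(both) | Share left out |
|---|---|---|
| 0 | 1.93% | 1 − 1.93/12.17 = 84% |
| 0.2 | 3.02% | 75% |
| 0.4 | 4.37% | 64% |
| 0.6 | 6.03% | 50% |

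The correlation drives the answer. Adding retest error (SD 1.5-3 ratio points and 4-6% predicted) changes the range to 52-83%.

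**3. Incident cases from retest noise alone.** Keep those assumptions and simulate two measurements per person with independent errors and no true change. Call a person incident under the GOLD row if the row is failed at the first measurement and met at the second. Over all pairings of the error limits and ρ from 0 to 0.6:

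- 25-52% of these apparent incident cases had a measured ratio below 0.70 at the first measurement. The low end has large ratio error and small FEV1 error; the high end is the reverse.
- Apparent incident cases make up 0.8-2.7% of the cohort under the GOLD row.
- Under a ratio-only rule (0.70 or above, then below 0.70) they make up about 2.9-5.8%. A ratio-only rule therefore produces more noise cases, which bears on the fix.

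**4. Counts with true change.** Take N = 6,000 from the protocol. Assume that ratio-only prevalence is 7.8% or 19.7% (the regional extremes in Background, used only as anchors because the survey's spirometric definition is not given); that 30-70% of low-ratio people have FEV1 at or above 80%; that 10-30% of those fall below 80% within four years; and that new low ratio arises at 0.5-1% per year, with the same 30-70% split by FEV1.

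- *Lowest:* 0.078 × 6,000 = 468 with a low ratio; 30% = 140 are non-cases; 10% = 14 progress. New cases: 5,532 × (1 − 0.99⁴) = 218, of whom 70% = 153 also have FEV1 <80%. Already obstructed: 14/(14 + 153) = 8%.
- *Highest:* 0.197 × 6,000 = 1,182; 70% = 827; 30% = 248 progress. New cases: 4,818 × (1 − 0.995⁴) = 96, of whom 30% = 29 also have FEV1 <80%. Already obstructed: 248/(248 + 29) = 90%.
- Prevalence would read 2.3-5.5% against 7.8% by ratio alone, or 5.9-13.8% against 19.7%. Low-ratio people would form 2.5% (140/5,672) to 14.7% (827/5,645) of the at-risk set.

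The 8-90% range shows that the documents do not fix the size once real change is allowed.

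**The case against.** The strongest reply is that this is a declared definition and not a mistake: the article names its source, prints both conditions and lists two alternatives. That stands in part. Ratio below 0.70 at any FEV1 is not the only meaning COPD can carry, so the prevalence limb concerns labelling and an added figure. It does not show that the printed number would be wrong. A reader might infer that Table 1 misstates its GOLD source; the source is not available here and the point does not rely on it.

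Second, a reader might infer that the plan definitely places people with a low ratio in the at-risk set. The article does not say so. It defines no risk set, its reference to Table 1 covers all three rows, and the ERS row is already ratio-only. The full protocol or analysis plan may settle this. The incidence limb is therefore conditional, and it concerns a secondary outcome. Change in lung function, the four-year primary outcome, needs no case definition, except where decline is described among COPD subjects identified in phase one.

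Third, counting by ratio alone yields more noise-only incident cases (step 3). That is correct and is a real cost of the fix. It does not remove the mixing of onset with progression.

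Finally, a reader might extend the point to the planned comparison with the earlier Latin American survey, since the Discussion describes similar methods "which will allow comparison of data between the Latin American countries studied in the PLATINO study and the baseline phase of the PRISA study" and Background says that survey "examined the prevalence of COPD by pre- and post-bronchodilator spirometry among persons over age 40 in five major Latin American cities", while this cohort is aged 45-75. The documents do not support a finding there. Nothing commits the authors to a crude comparison, age restriction or standardisation is routine analysis detail, and the survey's spirometric definition is not given.

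**Conclusion.** The point holds in a limited form. Followed as written, the GOLD row leaves people with ratio below 0.70 and FEV1 at or above 80% predicted out of the phase-one COPD prevalence. Unless the risk set is defined otherwise, it also lets them count later as incident COPD without new obstruction. The direction is certain and the size is not. With ratio mean 0.77, SD 0.06, FEV1 mean 95%, SD 15, correlation 0-0.6 and the stated retest error, about 50-85% of low-ratio people are left out and about 25-50% of noise-only incident cases already had a low ratio. Those inputs are assumptions; none comes from the documents. The change is worth making because it affects what the phase-one primary estimate and the incidence results mean, and it costs little.

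**What to change.** - **Prevalence.** Report post-bronchodilator FEV1/FVC <0.70 at any FEV1 alongside the Table 1 figure, and label the latter as ratio <0.70 plus FEV1 <80% predicted.
- **Incidence.** State which row of Table 1 applies. Restrict the risk set to participants with baseline ratio 0.70 or above, and report crossing 80% predicted among those already below 0.70 separately, as progression.
- **Sensitivity.** Because ratio-only incidence is more exposed to retest misclassification near 0.70, add an analysis that requires confirmation at a later measurement where one exists, or a minimum fall in the ratio. The Abstract places repeat measurements in year four, so confirmation may not be available for everyone and the minimum-fall version may be the workable one.

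Cost: outcome wording, one more set of results and one sensitivity analysis, all from spirometry already planned. No new visits or measurements are needed.
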